# **Methods and Procedures**

Patients attending COVID treatment center (YCM Hospital, Pimpri, Pune, India) of the investigators will be screened for their participation in the study. Patients should be COVID-19 positive, diagnosed recently. No discretion for enrollment will be made based on gender, color, religion and cast. Information about the study will be shared with the patients and their eligibility will be checked during screening. Those fulfilling this requirement and who are willing to participate will be given informed consent document and patient information sheet for reading. Adequate time will be given for reading the same and the same will be explained verbally. All questions will be answered to the patients’ satisfaction. Patient will be considered as enrolled only after consenting procedure is done.

Patients will be counseled about administration of IP (dose, timing, method etc.). In case of SAE / other event which necessitates to break the blind, it will be broken. Appropriate treatment will be provided and the IP might be discontinued if investigator thinks this in the best health interest of the participant.

Follow-Up:

After enrollment (Day 0), there will be one clinical and the next two: either telephonic or clinical follow-ups: first follow-up visit at day 5 (+1 day), second follow-up visit at day 15 (+2 days) and third follow-up visit at day 30 (+2 days).

Patients will need to make sure, there is no gap in consuming the IP.

Patients can call the study coordinator anytime for the queries if any.

Unscheduled Visits:

Patients will continue to visit his/her physician at the site for medical care with prior appointments for routine and regular check-ups. Study coordinator will try and combine their study follow-up visit with their regular visit at the site. Patients should, as far as possible, visit the site in case of medical emergencies.

Study Design:

This is a two arm, double blind, randomized, controlled, prospective study to determine safety and efficacy of Cap. IP in COVID-19 positive patients.

After enrollment, they will get the IP / Placebo in addition to their regular treatment they might be receiving for their condition. (2 capsules twice a day for prior 15 days and 1 capsule twice a day from day 16)

A total of 60 patients (Can be extendable to 150) will be enrolled in the study in different groups. The reason behind this sample size that, we can apply paired t test with adequate power for an exploratory study.

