# Study Rationale

COVID -19 is a respiratory illness that has led to a pandemic, affecting more than 200 countries in the world. Due to sudden advent and rapid spread of infection, no antiviral drug has been found to be effective since its onset.

1. While there is no medicine for COVID-19 as of now, enhancing the body’s defense system (immunity) plays an important role in maintaining optimum health and the IP (study drug) might possibly play an important role in enhancing immunity.
2. Role of study drug as an antiviral could also be tested.

The proposed trial is to check efficacy of Cap. IP in the management of COVID-19.

We intend to enroll up-to 75 COVID positive patients in the study. Eligible and willing patients will either get Cap. IP as an add-on therapy to the SOC (Standard of Care) or placebo (inert substance) as an add-on therapy to the SOC.

Aim: To assess the efficacy and safety of Cap. IP in the management of COVID 19 patients and also in boosting innate immunity.

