# Study Design

Overview of the Study Design

- This is a randomized, 2-arm, parallel group, double-blind, 1:1 ratio, controlled, exploratory trial with a study period of 30 days from the of enrolment.
- A total of up-to 75 known COVID-19 positive (with positive RT-PCR) patients will be enrolled in the study.
- All the patients enrolled in the study will get the Investigational Product (IP-1 and IP-2), or 2 capsule of Placebo in similar sized and colored bottles, two times daily for the 1^st^ 15 days. From 16^th^ day onwards patients will get one capsule twice daily i.e. IP-2 or capsule placebo up to day 30.
- Patients will undergo laboratory investigations upon enrolment and on last visit. RTPCR for COVID will be done on day 5 (+ 1 day).
- Patients and doctors treating will not be knowing what the participating subject has received. Subjects will be given coded bottles, containing dose for 30 days.
- No medicine which his/her physician is giving will be stopped. No modifications shall be suggested in their diet and daily routine physical activities.
- Thus, patients enrolled in the study will get the IP / Placebo in addition to the standard of care which they were already receiving at the time of enrolment.
- Half of patients will be getting Cap. IP and half will be getting Cap. Placebo throughout the study duration of 1 month.

Study period for enrolled patients will be 30 days:

- Enrollment (day 0): After Informed Consent Process, Demographics and other information for CRF will be recorded. Investigations: COVID 19 RTPCR, Lymphocyte subset analysis (TH1, TH2, Th17, IL6, NK Cells and CD markers); Immunoglobulin IGG (Serum); Immunoglobulin IGM (Serum); Liver Function Test and Kidney Function Test will be done. Cap. bottle will be given to the patients with the dose lasting for 30 days.
- Day 3±1: COVID-19 RT PCR (quantitative) test will also be conducted on day 3 (±1) on 5 subjects of each group
- Follow-up 1: Day (5±1): COVID-19 RT PCR (quantitative) test will be conducted for all subjects on Day (5±1). CRF will be filled for knowing the overall status.
- Follow up 2 (15^th^ day+ 2 days): This follow up will be clinical/telephonic. CRF will be filled for knowing the overall status.

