- Follow up 3 (30^th^ day+ 2 days): Patients will be followed up at day 30. This visit will be done telephonically. Patient will not visit site but blood investigations shall be carried out. Investigations will be done outside the site, considering that the site is COVID specific hospital. The investigations are; Lymphocyte subset analysis (TH1, TH2, Th17, IL6, NK Cells and CD markers); Immunoglobulin IGG (Serum); Immunoglobulin IGM (Serum); Liver Function Test and Kidney Function Test will be done. All the unused IP will be collected.
- Sponsor will provide 10 codes (5 from each, IP and placebo, not mentioning which is placebo and IP). These will get Sr. Ferritin, CRP and D- Dimer done for same patients on day 0.

Every time subject coming to the scheduled follow-up should be asked to bring the remaining capsules with the bottle.

Flow chart

Screening

(I/E Criteria, ICF reading)

Enrollment (Day 0) Randomization

IP Arm Placebo Arm (30 patients in each arm)

(Consenting, Clinical Exam, Investigations, QOL, IP / Placebo Dispense)

COVID-19 RT PCR (quantitative) test on day 3 (±1) for 5 subjects of each group

1^st^ Follow-up: Day (5±1)

COVID-19 RT PCR (quantitative)

2^nd^ Follow-Up: Day (15+2)

[Clinical/telephonic]

3^rd^ Follow-Up: Day (30+2)

[Tele follow-up Blood Investigations at lab]

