**Results are rounded up to the nearest integer**

**Results from OpenEpi, Version 3, open source calculator –SSC cohort.**

Considering drop-outs, a total of up-to 75 (but more than 60) subjects in total will be considered.

Study Population:

COVID-19 positive subjects.

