# Randomization Process:

An alphanumeric coded set of IP/Placebo containers will be used. Participants will be automatically randomized to two groups in the ratio 1:1. Blind will be broken after the last follow-up of last enrolled subject is over.

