Subjects, investigator staff and personnel performing the study assessments will remain blinded to the identity of the treatment from the time of randomization. Monitoring will be done by unblinded personnel from sponsor.

Following measures will be applied to keep required personnel blinded.

1. Sponsor will provide coded bottles containing IP or placebo in those.
2. The list of which bottle contains what will not be shared with any site member or with the CRO.

Adverse Events:

Very serious [allergic reaction](http://www.webmd.com/allergies/anaphylaxis-15/slideshow-allergy-triggers) to this drug should be rare. However, patient will be asked to seek immediate medical attention if he/she notices any symptoms of a serious allergic reaction, including: [rash](http://www.webmd.com/skin-problems-and-treatments/guide/common-rashes), [itching](http://www.webmd.com/skin-problems-and-treatments/guide/skin-conditions-pruritus)/swelling, severe [dizziness](http://www.webmd.com/first-aid/understanding-dizziness-basics), [trouble breathing](http://www.webmd.com/lung/breathing-problems-causes-tests-treatments).

Of particular interest, these drugs are generally regarded as safe.

Reporting of the adverse events will be done in following format:

1. Patient Details:

Initials and other relevant identifier (PID)*

Gender:

Age:

Weight:

Height:

1. Suspected Drug(s)

Generic name of the drug(s)*

Indication(s) for which suspect drug was prescribed or tested

Dosage form and strength

Daily Dose and Regimen

Route of administration

Starting date and time of day

Stopping date and time of day or duration of treatment

1. Other Treatment(s)

The same information for concomitant drugs (including non-prescription/OTC drugs) and non-drug therapies, as for the suspected drug(s) will be provided.

1. Details of Suspected Adverse Drug Reaction(s)

Full description of reaction(s) including body site and severity, as well as the criterion (or criteria) for regarding the report as serious will be provided. In addition to a description of the reported signs and symptoms, whenever possible, a specific diagnosis for the reaction will be described.*

Start date (and time) of onset of reaction

Stop date (and time) or duration of reaction

De-challenge and re-challenge information

Setting (e.g., hospital, out-patient clinic, home, nursing home)

1. Outcome

Primary Outcome:

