# Data Analysis

Overall blinding will be broken at 30 days i.e.at the end of the study. Depending upon ADRs / SAEs, individual blinding might be broken on case-to-case basis.

Paired t test and any other appropriate test will be applied for analysis.

As this is intent-to-treat design, all the data, even the dropped-out patients’ and lost to follow-up patient’s collected data will be analyzed.

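### The protocol sets enrolment at 60 with an open extension to 150, against a cap of 75 elsewhere, and does not exclude an extension made with knowledge of results

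*Protocol*

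**What the plan says.** The Protocol states the total in five places.

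- Study Rationale: "We intend to enroll up-to 75 COVID positive patients in the study".
- Study Design, overview: "A total of up-to 75 known COVID-19 positive (with positive RT-PCR) patients will be enrolled in the study".
- Study Design, flow chart: "IP Arm Placebo Arm (30 patients in each arm", that is, 60 in all.
- Methods and Procedures: "A total of 60 patients (Can be extendable to 150) will be enrolled in the study in different groups".
- Text after the OpenEpi sample-size table, which refers to drop-outs without giving a rate: "a total of up-to 75 (but more than 60) subjects in total will be considered".

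The table itself gives 56 (Kelsey) or 54 (Fleiss).

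On blinding, Study Treatment (f) says: "Monitoring will be done by unblinded personnel from sponsor". Ethical Considerations (d) lists monitors among those with access to enrolled patients' data and leaves the unblinding list with the sponsor. The paragraph on data and monitoring gives the monitor access to study documents. The list is withheld from the site and the CRO.

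On timing, Randomization Process says: "Blind will be broken after the last follow-up of last enrolled subject is over". Data Analysis says: "Overall blinding will be broken at 30 days i.e.at the end of the study".

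**The concern.** A trial needs one target size, and any change to it should be independent of the accumulating treatment comparison. Here two pairs of statements cannot both be true: 60 against more than 60, and 150 against a cap of 75. Nothing says what would trigger the move to 150, who would decide it, or on what data.

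The blinding arrangements make this gap matter more. Within the sponsor, the same monitors may know the treatment and see patient data, and no passage keeps them away from a decision on size. If enrolment were continued because the result was not yet significant, the false-positive rate would rise above the nominal 5%. Even if nobody did so, the trial could not show from its protocol that the final size was independent of the results.

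**Working it through.** **1. Reproduce the protocol's calculation.** Inputs from the sample-size table: 5% of the unexposed and 35% of the exposed with the outcome, two-sided 5% level, 80% power, ratio 1. The mean proportion is 0.20 and the difference is 0.30.

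- Kelsey: n per arm = (1.960 + 0.842)² × 2 × 0.20 × 0.80 / 0.30² = 27.91, rounded up to 28, total 56.
- Fleiss, without continuity correction: n per arm = [1.960 × √(2 × 0.20 × 0.80) + 0.842 × √(0.05 × 0.95 + 0.35 × 0.65)]² / 0.30² = 26.70, rounded up to 27, total 54.

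Both match the table. The arithmetic is not in dispute.

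**2. Can drop-out link 54–56 to the stated totals?** Implied drop-out = 1 − (calculated size / stated total).

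| Stated total | From 54 | From 56 |
| --- | --- | --- |
| 60 | 10.0% | 6.7% |
| 75 | 28.0% | 25.3% |
| 150 | 64.0% | 62.7% |

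Drop-out could explain 60 or 75, although no rate is stated. It cannot plausibly explain 150, which is twice the cap (150 / 75 = 2) and about 2.7 times the calculated size (150 / 56 = 2.7).

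**3. Is 150 needed for power?** With the protocol's 5% and 35%, and every enrolled patient evaluable, power is 84.6% at 60, 91.8% at 75 and 99.8% at 150. The stated assumptions give no reason for 150. The sentence that follows the figure in Methods and Procedures appeals to a paired t test, but gives no difference or standard deviation from which 150 could be derived.

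**4. What could a result-driven extension cost?** The protocol defines no looks, so the schedules below are assumptions. Each look tests at nominal two-sided 5%, and enrolment continues only if the result is not significant. Under the null, the test statistics at totals n₁ < n₂ are standard normal with correlation √(n₁/n₂). The error is the probability that any of them exceeds 1.96 in absolute value.

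| Assumed looks | Correlation | Two-sided type I error |
| --- | --- | --- |
| One fixed total | – | 5.0% |
| 60, then 75 | √(60/75) = 0.894 | about 7.1% |
| 60, then 150 | √(60/150) = 0.632 | about 8.6% |
| 60, 75 and 150 | 0.894, 0.632, √(75/150) = 0.707 | about 10.1% |

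**5. Do the blinding passages close the gap?** Randomization Process and Data Analysis govern when the blind is broken overall. They do not restrain sponsor personnel who are unblinded from the start. The 30 days in Data Analysis is also each patient's own study period, so that sentence can be read differently from the one in Randomization Process, which refers to the last enrolled patient. While the total is open, the last enrolled patient is not defined either.

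**The case against.** Much can be said for the protocol. A cap of 75 and a range of more than 60 up to 75 are compatible, and the flow chart's 30 per arm is the same 60 as in Methods and Procedures. A reader might count four incompatible totals, but there are only two real conflicts. One of them, 60 against more than 60, is close to a slip at the boundary.

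A reader might also infer that the sponsor intends to extend on the results, or that the trial's true error rate is 8.6% or 10.1%. The document supports neither. It plans no interim look, names no one who would decide on an extension, and calls the trial exploratory, which lessens the weight of strict error control. The inflated rates belong to assumed schedules. The handling of alpha may also stand in a statistical analysis plan that is not at hand, so its absence here is not counted.

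It would likewise go too far to say that the double blind is defeated. Participants, investigator staff and assessors stay blinded, and the viral-load part of the primary outcome is a quantitative RT-PCR that monitoring queries would hardly affect. Early recovery is more exposed.

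What the objection does not remove is 150 against 75, the missing basis and rule for extending, and unblinded monitors with access to patient data.

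**Conclusion.** The point holds as an internal contradiction with an open safeguard. The current text gives 60 against more than 60, and 150 against a maximum of 75. From 54 to 56 patients, 150 would imply about 63% to 64% drop-out, and no rule governs the extension. Because unblinded sponsor monitors can see patient data and the sponsor holds the codes, the protocol does not exclude an extension made with knowledge of results. It does not show that one is planned.

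The contradiction and the drop-out figures follow from the protocol alone. The error rates of about 7.1%, 8.6% and 10.1% hold only under the assumed looks at nominal 5%, and that a decision-maker would sit within the sponsor is a possibility, not a statement in the text. In an exploratory trial this should be corrected, but it does not invalidate the design.

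**What to change.** 1. State one fixed randomised total in Study Rationale, Study Design (overview and flow chart), Methods and Procedures and the sample-size text. A ceiling is not enough: stopping anywhere between 60 and 75 would stay open. Give the drop-out rate that leads from 54–56 to that total. A total of 75 implies about 25% to 28%, which the protocol would have to state as its own assumption.
2. Delete the extension to 150. Alternatively, allow an increase only by amendment, decided by people without access to treatment codes and on pooled blinded data.
3. Have blinded staff do the monitoring, and leave the code list with a sponsor person who has no access to outcome data.
4. Align the 30-day wording in Data Analysis with Randomization Process, which already ties unblinding to the last follow-up of the last patient.

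The cost is amendment wording and a reassignment of monitoring roles. The sponsor also gives up an open-ended extension.

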**Sample size: Cross- sectional, Cohort and Randomized Clinical Trials**

| Two sided significance level ( 1 alpha) | 95 |
| --- | --- |
| Power ( 1-beta. % chance of detecting) | 80 |
| Ratio of sample size, Unexposed/ exposed | 1 |
| % of Unexposed with outcome | 5 |
| % of Exposed with outcome | 35 |
| Odds ratio | 10 |
| Risk/ Prevalence ratio | 7 |
| Risk/ Prevalence | 30 |

|  | Kelsey | Fleiss |
| --- | --- | --- |
| Sample Size Exposed | 28 | 27 |
| Sample Size Non exposed | 28 | 27 |
| **Total Sample Size** | **56** | **54** |

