- Efficacy of the herbal extracts in COVID 19 positive patients (in declining viral load: time-point: 5 days and early recovery)

Secondary Outcomes:

- - Efficacy of the herbal extracts as an immune-modulator - TH1, TH2, Th17, IL6, NK Cells and CD markers; Immunoglobulin IGG (Serum); Immunoglobulin IGM (Serum): at 30 days.
  - Efficacy of the investigational product in reducing sequela of the disease
  - Safety analysis (Liver Function Test and Kidney Function Test) including serious allergic reaction of: rash, itching/swelling, severe dizziness, trouble breathing.

1. Details about the Investigator*

Name

Address

Telephone number

Profession (specialty)

Date of reporting the event to Ethics Committee:

Signature of the Investigator

Information marked ‘*’ must be provided.

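### The 80% power is calculated for an unnamed yes/no outcome (5% versus 35%), not for the primary outcome or the test the protocol names

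*Protocol*

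**What the plan says.** The sample-size table in the protocol takes these inputs:

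- significance: "Two sided significance level ( 1 alpha) | 95"
- power: "Power ( 1-beta. % chance of detecting) | 80"
- allocation: "Ratio of sample size, Unexposed/ exposed | 1"
- control rate: "of Unexposed with outcome | 5"
- treated rate: "of Exposed with outcome | 35"

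The result is 28 per arm (Kelsey, 56 in total) or 27 per arm (Fleiss, 54 in total), taken from the cohort module of OpenEpi. The protocol then adds: "Considering drop-outs, a total of up-to 75 (but more than 60) subjects in total will be considered". The flow chart shows 30 per arm.

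Immediately before the table, under Methods and Procedures, a different reason is given: "The reason behind this sample size that, we can apply paired t test with adequate power for an exploratory study". The Data Analysis section names the paired t test as well, and otherwise leaves the choice of test open.

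The primary outcome is listed as "Efficacy of the herbal extracts in COVID 19 positive patients (in declining viral load: time-point: 5 days and early recovery". The Study Design section and the Study Assessment Table have the day-5 RT-PCR as a quantitative test in all subjects. Early recovery is not defined. The primary objective, stated separately, concerns innate immunity.

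**The concern.** A power figure means something only for a stated outcome, effect and test. Here the table, the written justification, the named test and the primary outcome do not fit together:

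- The table needs a yes/no event and a comparison of proportions. The protocol names no such event and gives no source for 5% or 35%.
- A paired t test needs a mean change and its SD. Neither is given.
- A paired t test asks whether patients changed from day 0 within one arm. It does not estimate the difference between product and placebo, which is what randomisation is for.

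The risk lies in interpretation. If the trial finds no difference in viral load, a reader could take that as evidence from a trial with 80% power, which the protocol does not establish for that outcome.

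**Working it through.** **1. Reproduce the protocol's figure.** Inputs from the table: p0 = 0.05, p1 = 0.35, difference 0.30, mean rate 0.20, z = 1.960 (two-sided 5%) and 0.842 (80% power).

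- Kelsey: n = (1.960 + 0.842)² × 2 × 0.20 × 0.80 / 0.30² = 7.849 × 0.32 / 0.09 = 27.9, so 28 per arm.
- Fleiss, no continuity correction: n = [1.960 × √(2 × 0.20 × 0.80) + 0.842 × √(0.05 × 0.95 + 0.35 × 0.65)]² / 0.30² = (1.109 + 0.441)² / 0.09 = 26.7, so 27 per arm.
- Odds ratio (0.35/0.65)/(0.05/0.95) = 10.2 and risk ratio 0.35/0.05 = 7.0 agree with the table's 10 and 7.

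The arithmetic is right. What matters is what it is attached to.

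**2. Set the elements side by side.**

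| Element | Type of outcome | Comparison |
|---|---|---|
| Sample-size table | yes/no, unnamed | between arms |
| Reason given for the size | continuous (paired t test) | within arm |
| Test named in Data Analysis | continuous (paired t test) | within arm |
| Primary outcome | quantitative viral load at day 5, plus undefined early recovery | not stated |

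The table's outcome type matches neither the named test nor the quantitative part of the primary outcome.

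**3. What the size delivers if the endpoint is change in viral load.** The protocol gives no mean difference or SD, so the result can only be stated in SD units of the change. For a two-sample t test, two-sided 5%, 80% power, the detectable difference is roughly 2.80 × √(2/n). At n = 30 this gives 0.72, and the exact noncentral-t value is slightly larger. Exact values:

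| Evaluable per arm | Where the number comes from | Detectable difference |
|---|---|---|
| 28 | Kelsey result | 0.76 SD |
| 30 | flow chart | 0.74 SD |
| 37 | 75 enrolled, no drop-out | 0.66 SD |

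Power at 30 per arm for assumed differences of 0.3 / 0.4 / 0.5 / 0.6 / 0.8 SD is 21% / 33% / 48% / 63% / 86%. At 0.5 SD it is 45% with 28 per arm and 56% with 37.

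**4. What the size delivers if a yes/no endpoint is meant.** Power of Fisher's exact test is the sum, over all pairs of counts with p ≤ 0.05, of Bin(a; n, 0.05) × Bin(b; n, 0.35). It is 74% at 28, 79% at 30 and 90% at 37 per arm. By the normal approximation without correction, power is 82%, 85% and 91%. The test therefore has to be named along with the event.

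The unsourced control rate matters too. As an illustration only, keep the 30-point difference and assume a control rate of 20% to 40%. Power by the normal approximation at 30 per arm is then 65% to 69%, and 39 to 42 per arm would be needed.

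**5. Why a paired test does not serve.** Suppose viral load falls by an assumed 0.5 SD of the change in 30 placebo patients, with no active treatment. A paired t test in that arm alone is significant 75% of the time. At an assumed 1 SD it is significant almost always (over 99.9%). Significance within an arm therefore says nothing about the product.

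**The case against.** The strongest reply is that the outcome behind the table may belong to the trial after all. A reader might infer from the mismatch that the 80% applies to no analysis in the trial, or that the table's event is certainly not the primary outcome. The documents do not support that. Early recovery, or a negative RT-PCR at day 5, could be analysed as yes/no, and the Data Analysis section leaves room for a comparison of proportions. What can be said is narrower: the protocol names neither such an event nor such a test.

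A reader might also infer that the trial is too small even on its own inputs, because a continuity-corrected formula gives 34 per arm (68 in total), above the 60 in the flow chart. This fails as well. The protocol allows up to 75, 68 lies within that, and Fisher's exact test has 86% power at 34 per arm. An uncorrected formula, correctly applied, is not an error.

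Nor should the change a paired test can detect within one arm be read as the between-arm effect the sponsor expects. The protocol proposes no such effect.

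Finally, the protocol calls the trial exploratory. That would justify making no power claim and lowers the weight of this point. It does not justify keeping an 80% figure for an event nobody has named.

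**Conclusion.** The point stands as a mismatch between the sample-size basis and the planned analysis, not as a calculation error. The protocol's 28 and 27 per arm reproduce, but the 80% is tied to no outcome or analysis the protocol names, the 5% and 35% have no stated source, and the paired t test offered as justification does not compare the arms.

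For a between-arm t test on change in viral load, the planned size has 80% power only for a difference of about two-thirds to three-quarters of an SD. This rests on three assumptions: the endpoint is continuous and roughly suited to a t test, the patients counted are evaluable, and the effect sizes used in the power range are illustrative.

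The fault does not bias the treatment estimate. In an exploratory trial it should be fixed but does not rank as critical.

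**What to change.** First decide and state the primary endpoint and the test that compares product with placebo on it. Remove the paired t test with adequate power as the reason for the size. Then replace or complete the table in one of two ways:

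- **If the endpoint is change in viral load from baseline to day 5:** drop the 5%/35% table and state, for example: With 28 / 30 / 37 evaluable patients per arm, a two-sample comparison has 80% power (two-sided 5%) for a difference of 0.76 / 0.74 / 0.66 SD of the change; smaller effects will be reported as estimates with 95% confidence intervals.
- **If a yes/no endpoint is meant:** define it, give the source of the 5% and 35%, name the test and state its power, for example Fisher's exact test with 74% / 79% / 90% at 28 / 30 / 37 per arm.

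The cost is protocol wording. No patients are added. For viral load, the protocol would claim sensitivity to large differences only.
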